**Table 2: Sample size required to detect superior completion of 2R_20_ or 2R_30_ compared to 4R_10_**

| Completion rate | | Number required per group to detect significant difference*. | | | |
| --- | --- | --- | --- | --- | --- |
| **4R_10_** | **2R_20_ or 2R_30_** | N per arm – non-HHC | N per arm –HHC | N per arm – mixed | Total N  (3 arms) |
| 70% | 75% | 1248 | 2484 | 2075 | 6226 |
|  | 80% | 290 | 578 | 483 | 1450 |
|  | 85% | 118 | 235 | 196 | 589 |
| **75%** | 80% | 1091 | 2172 | 1815 | 5446 |
|  | **85%** | **247** | ***493*** | ***412*** | ***1237*** |
|  | 90% | 97 | 193 | 151 | 453 |
| 80% | 85% | 903 | 1797 | 1505 | 4515 |
|  | **90%** | 196 | 391 | 306 | 917 |
|  | 92.5% | 115 | 230 | 180 | 540 |

**Power = 80% and alpha = 0.05. The calculation of total number required is based on 3 assumptions: (i) 65% of all enrolled subjects will be Household Contacts (HHC), and 35% will be other risk groups, as was seen in our recently completed 4R trial; (ii) The intra-class correlation coefficient (ICC) or clustering effect of households on completion will be 0.33 – as was demonstrated among study subjects who had at least one other family member in the 4R vs 9H study; (iii) We will use 4 as estimated average number of household contacts, based on two systematic reviews (Morrison J, Pai M, and Hopewll PC 2008; Fox GJ et al. 2013).*

In the 4R vs 9H trials, 78% of adult participants in the phase 2 trial (Menzies D et al. 2008), and the phase 3 trial (Menzies et al. 2018) completed the 4-month regimen. Assuming a similar rate of completion in this planned trial of 75%, then we would need to enroll **412** participants into each arm to detect a 10% better completion rate. Allowing for a 10% withdrawal, or otherwise not analyzable participants, this would inflate the number per arm to 453, so we plan to enroll a total of **1359** participants. As seen above, this number would provide limited power to detect smaller differences in completion. For example, 1815 participants per arm would be needed to detect a 5% better completion rate.

The approximate anticipated number of participants enrolled in each study site is as follows: 100 in Calgary, 100 in Edmonton, 100 in Montreal, 150 in Greater Vancouver (Canada); 500 in Bandung (Indonesia), and 450 in Ho Chi Minh City (Vietnam). Enrollment will be closed when the target 1359 is reached.

**For the primary outcome of safety:** Grade 3-4 Adverse events considered possibly/probably related to study drug:

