- Active TB – the incidence of active TB (microbiologically confirmed and all forms) in the 26 months post-randomization per 100 person-years of follow-up will be compared between all three arms.

All analyses will include adjustment for clustering by household. In stratified analysis, results will be presented by indication for LTBI treatment. Sensitivity analyses will be conducted where by analysis are stratified by study centre and by country.

Interim analyses

To optimize protection of safety of study participants, we plan at least two interim analyses of study regimen completion and of Grade 3-5 adverse events. The first analysis will be conducted after the first 150 participants randomized (i.e. approximately 50 in each arm) have completed therapy. This means we will assess outcomes that have occurred in each of these individuals up to 146 days post-randomization. The second interim analysis will be conducted 146 days after randomization of the 450^th^ Participant – i.e. after approximately 150 participants should have completed therapy in all 3 arms. However, as described below, the 2^nd^ analysis may be performed sooner if there are concerns about excess toxicity with either high-dose arm.

Our goal is to identify as early as possible if the high dose rifampin regimens are associated with a clinically important increased rate Grade 3-5 AE, or intolerance – defined as failure to complete therapy. The study bio-statistician will conduct both interim analyses in a blinded fashion. Given that there are two planned interim analyses, the p value -adapted for multiplicity of testing- that will be used to consider significant the difference between proportions is of p<0.022 (Pocock’s method).The Data Safety and Monitoring Board (DSMB – see below for more details) will also consider results while remaining blinded to the identity of the regimens. For each interim analysis, if any of the regimens meets criteria for a clinically important difference in adverse events or completion, then we will unblind in step-wise fashion. If unblinding is deemed necessary, the person in charge of code breaking will be the principal investigator ([name]) and the study coordinator ([name]). Same procedures will be followed if DSMB asks for unblinding in specific cases for serious and unexpected adverse events.

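### Completion is sized at alpha 0.05, but the interim section sets p<0.022 without limiting it to the interims, so the plan implies two thresholds for a primary outcome

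*Protocol*

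**What the plan says.** The note to Table 2 (Sample size considerations) gives "Power = 80% and alpha = 0.05". For 4R10 at 75% and a high-dose arm at 85%, the table gives 247 per arm without clustering, 493 if all are household contacts, and 412 for the planned mixture. The text below it takes 412 "participants into each arm to detect a 10% better completion rate" and raises this to 453 per arm (1359 in total) for 10% loss. That section mentions neither the interim looks nor any level other than 0.05.

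Under Statistical analysis, Interim analyses, the protocol says "we plan at least two interim analyses of study regimen completion and of Grade 3-5 adverse events". The first comes "after the first 150 participants randomized (i.e. approximately 50 in each arm) have completed therapy", and the second at about 150 per arm. It continues: "Given that there are two planned interim analyses, the p value -adapted for multiplicity of testing", and the level "that will be used to consider significant the difference between proportions is of p<0.022", with Pocock's method named as the source.

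The description of the primary completion analysis compares the completion proportion in each high-dose arm with the standard arm and states no significance level.

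**The concern.** Completion is both a primary outcome and one of the two outcomes examined at the interims, and its analysis is a difference between proportions. A reader looking for the level of the final completion test finds 0.05 in one section and 0.022 in another, and nothing that says which applies.

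The choice matters. A final p-value between 0.022 and 0.05 would be a success under the sample-size section and a failure under the literal wording of the interim section. The protocol says that without significantly superior completion the case for pursuing the two-month regimens is weaker, and its Rationale section makes better completion part of the justification for a phase 3 trial. Participants and staff know the treatment duration, so the threshold should not be left to be chosen once the results are known.

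**Working it through.** **Inputs (all from the protocol).** Completion 75% and 85%; power 80%; alpha 0.05, or 0.022 from the interim section; intra-class correlation 0.33; 4 contacts per household; 65% household contacts; 412 analysable and 453 enrolled per arm. The protocol does not state the sidedness of the 0.05; step 1 settles it.

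**1. Reproduce Table 2.** With unpooled variance, n = (z_alpha + z_power)² × [p1(1−p1) + p2(1−p2)] / (p1−p2)².
- The variance term is 0.1875 + 0.1275 = 0.315.
- Two-sided 0.05: (1.960 + 0.842)² × 0.315 / 0.01 = 247, as stated.
- One-sided 0.05 gives 195, so the table rests on a two-sided test.
- Household contacts: design effect 1 + 3 × 0.33 = 1.99, so 247.2 × 1.99 = 492 (stated 493).
- Mixture: 247.2 × (1 + 0.65 × 0.99) = 247.2 × 1.6435 = 406 (stated 412, a ratio of 412/247 = 1.668). The gap is below 2%. Both ratios are carried forward.

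**2. Identify 0.022.** Pocock's nominal two-sided level for an overall 0.05 with equally spaced looks, found by simulating the joint normal test statistics, is 0.0293 for two looks and 0.0222 for three. Used at three equal looks, 0.022 gives an overall error of about 0.05; at two it gives about 0.038. The protocol's figure therefore counts the final analysis as the third look.

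**3. Power at each level.** Power = Φ(0.10 / √(0.315/n_eff) − z_alpha), where n_eff is the number per arm divided by the design effect, and z is 1.960 at 0.05 and 2.290 at 0.022.

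| Per arm | Design effect | n_eff | Power at 0.05 | Power at 0.022 |
|---|---|---|---|---|
| 412 | 1.668 | 247.0 | 80.0% | 69.5% |
| 412 | 1.6435 | 250.7 | 80.5% | 70.2% |
| 453 | 1.668 | 271.6 | 83.6% | 74.1% |
| 453 | 1.6435 | 275.6 | 84.1% | 74.8% |

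For the first row: 0.10/√(0.315/247) = 2.800; 2.800 − 2.290 = 0.510; Φ(0.510) = 0.695.

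**4. Size needed at 0.022.** (2.290 + 0.842)² × 31.5 = 309 per arm before clustering. After clustering this is 309 × 1.6435 = 508, or 309 × 1.668 = 515. With the protocol's own inflation (412 × 1.1 = 453) these become about 559 to 567 per arm, or roughly 1,680 to 1,700 in total against 1359.

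**5. Width of the disputed zone.** With n_eff = 247 the standard error is √(0.315/247) = 0.0357. The smallest observed difference that reaches significance is 1.960 × 0.0357 = 7.0 points at 0.05 and 2.290 × 0.0357 = 8.2 points at 0.022. An observed gain between those values passes one section and fails the other.

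**The case against.** The strongest reply is that 0.022 was never meant for the final test. The sentence sits under Interim analyses, in a paragraph about detecting excess Grade 3-5 events or poor completion, between the statistician's conduct of the two interims and the DSMB's review. The final test is not named. Nor does the protocol describe an early success: the interim actions are dropping an arm or stopping enrolment for harm or worse completion, and if the standard arm is the worse one, enrolment to all three arms continues. With no early superiority claim, a final test at two-sided 0.05 needs no Pocock correction, and 80% is right. A statistical analysis plan may also fix the final level.

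Much of this stands. The layout fits an interim-only reading, and the 70% is conditional on the other one. What remains is that the protocol itself fixed a number without stating its scope, and that number is the method's constant only if the final analysis is counted.

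Two stronger readings are tempting but unsupported. A reader might infer that the sample size is miscalculated; the 75% against 85% row reproduces at its stated alpha. A reader might also infer an inflated overall error, since three tests at 0.022 at the actual, unequal look times (150, 450 and 1359 participants) give about 5.7%. That figure applies only if all three looks can declare a difference, and the protocol describes no early declaration of superiority.

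**Conclusion.** The protocol implies two thresholds for primary completion, two-sided 0.05 and 0.022, and does not reconcile them. If 0.022 governs the final test, as Pocock's method implies, power for 75% against 85% is about 70% with 412 analysable per arm and 74% to 75% with all 453, against the stated 80%. If it is confined to the interims and the final test is at 0.05, the 80% holds. The text does not settle which was intended, so it cannot be said outright that the trial is underpowered. The figures rest on the protocol's own completion rates, intra-class correlation, household size and share of household contacts, on the unpooled normal approximation that reproduces its table, and on counting only the final look as a success. This is an inconsistency between sections and not an arithmetic error.

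**What to change.** Add one sentence to the interim section, and carry it into the statistical analysis plan: the interim analyses cannot declare superiority, p<0.022 applies only to interim comparisons, and each final completion comparison is tested at two-sided 0.05. Add the word two-sided to the note to Table 2. This costs no participants and leaves the 80% intact.

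If 0.022 is intended for the final test, say so in the primary analysis section and restate the power in the sample-size section as about 70% with 412 analysable per arm. Keeping 80% at that level would need about 508 to 515 analysable per arm. Either choice should be made before any unblinded comparison of completion is seen.

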Most clinical trial experts do not suggest formal statistical stopping rules for safety. Instead, the DSMB will receive frequent safety reports and will “make judgments about the strength of the evidence and the absolute magnitude and seriousness of any safety signals” (Pocock, Clayton, and Stone 2015). As approximate guidance, we will suggest to the DSMB that for the 1^st^ interim analysis non-completion must be at least 10% worse and/or grade 3-5 adverse events more than 10% more frequent than the standard arm. For the 2^nd^ interim analysis occurrence of grade 3-5 adverse events would have to be 7.5% worse, and treatment completion at least 7.5% worse to consider dropping that arm. Grade 3-5 adverse events are very uncommon events with 4R (1-2% in our prior trials), meaning that we expect zero or only one AE in the standard arm with 50 participants. Hence occurrence of Grade 3-5 AE in only 5 or 6 of the first 50 participants randomized to either experimental arm would result in an AE rate difference of 10% for the 1^st^ interim analysis. This could happen due to chance alone. At the 2^nd^ interim analysis – we expect 2-3 persons with Grade 3-5 AE among the 150 randomized to 4R_10;_ to detect a difference of 5%, would mean at least 9-10 participants in the highest dose arm would have to have Grade 3-5 AE, or 18-20 participants with these AE in both high dose arms, before stopping the trial; this number with AE would be very unlikely due to chance alone. But, as noted above – these are guidelines only that will be suggested to the DSMB. The decision to stop enrolment to one or both experimental arms will be based not only on these differences, but also how serious the adverse events are. The threshold to stop will be lower if the events are more serious. As well, the DSMB can request more frequent analyses of adverse events – if there is any evidence on greater rate of AE with the higher dose arms.

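### The second-interim guidance on dropping an arm is inconsistent: a 7.5% threshold with an event count worked at 5%, and criteria joined by *and* where the rest of the section uses *or*

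*Protocol*

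**What the plan says.** All of this is in the protocol, Statistical analysis, under Interim analyses.

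- **Goal.** The interim looks are meant to find, as early as possible, a "clinically important increased rate Grade 3-5 AE, or intolerance". The two outcomes are joined by *or*. The later text on step-wise unblinding, and on what follows if a high-dose arm looks worse, also uses *or*.
- **First look, about 50 per arm.** The suggested guidance is that "non-completion must be at least 10% worse and/or grade 3-5 adverse events more than 10% more frequent than the standard arm". The example follows: "Hence occurrence of Grade 3-5 AE in only 5 or 6 of the first 50 participants randomized to either experimental arm" is said to give a 10% difference, against zero or one event in the standard arm.
- **Second look, about 150 per arm.** The guidance is that "occurrence of grade 3-5 adverse events would have to be 7.5% worse, and treatment completion at least 7.5% worse to consider dropping that arm". The example then says "we expect 2-3 persons with Grade 3-5 AE among the 150 randomized to" the standard arm, and that "to detect a difference of 5%, would mean at least 9-10 participants in the highest dose arm would have to have Grade 3-5 AE" before the trial is stopped; for both high-dose arms together the count is 18-20 events.
- **Significance level.** The p value "used to consider significant the difference between proportions is of p<0.022", by Pocock's method for two interim analyses.
- **Status.** The figures are described as approximate guidance only. Seriousness of events also counts, the threshold is lower for more serious events, and the DSMB can ask for more analyses.

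**The concern.** The first-look example turns its percentage threshold into an event count that a DSMB can apply. The second-look example appears to do the same job but starts from a different percentage. A DSMB member holding the paragraph would have two answers for one look: act at about 9-10 events, or at about 14-15.

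Separately, the second-look sentence, taken literally, asks for an adverse event excess and also for worse completion. The protocol expects the two-month arms to complete better because they are shorter, and it sizes the trial for 85% against 75%. The added condition is therefore one that the design expects not to be met, so an arm with excess toxicity could fall short of the literal guidance.

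These are the only numerical safety criteria for dropping an arm, and the participants are otherwise healthy people on two or three times the standard dose.

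**Working it through.** **Inputs from the protocol.** Standard-arm Grade 3-5 rate 1-2%; about 50 and 150 per arm at the two looks; 2-3 expected control events at the second look; thresholds of 10%, 7.5% and 5%; control completion 75%; planned completion in the two-month arms 85%.

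**Step 1: reproduce the event counts.** Count in one high-dose arm = expected control events + n x difference.

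- First look: 50 x 10% = 5. Adding 0 to 1 gives 5-6. This reproduces the stated count at the stated threshold.
- Second look at 5%: 150 x 5% = 7.5. Adding 1.5 to 3 control events (1-2% of 150) gives 9.0 to 10.5. This reproduces 9-10, and twice that is 18-20. In observed terms, (9 - 2)/150 and (10 - 3)/150 are both 4.7%.
- Second look at 7.5%: 150 x 7.5% = 11.25. Adding 2 to 3 gives 13.25 to 14.25, so 14-15 events, or 28-30 in both arms. With 1.5 expected control events the count would be 13.

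The stated 9-10 fits only 5%. An arm with 10 events against 2, a 5.3% difference, satisfies the example and fails the threshold.

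**Step 2: does the difference matter?** Exact binomial calculation, 150 per arm, independent participants, control rate 2%. The protocol gives no high-dose rate for this purpose, so a range is shown.

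| True high-dose rate | P(observed excess at least 5%) | P(observed excess at least 7.5%) |
| --- | --- | --- |
| 7% | 49% | 13% |
| 10% | 87% | 54% |
| 12% | 96% | 79% |

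**Step 3: *and* against *or* at 7.5%.** Simulation with 150 per arm, rates 2% and 10%, every event counted as a non-completion, and no clustering. Control completion of 75% can be taken among those without an event (73.5% overall, from 0.98 x 75%) or overall (76.5% among those without an event, from 75%/0.98). Both are shown.

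| Completion among other high-dose participants | Control 75% applies to | Met under *and* | Met under *or* |
| --- | --- | --- | --- |
| 75% | those without an event | 26% | 65% |
| 75% | all | 33% | 70% |
| 85% | those without an event | 1.5% | 54% |
| 85% | all | 2.9% | 54% |

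Under the first control convention, a 12% high-dose rate gives 43% against 85% (other participants completing at 75%) and 3.8% against 79% (at 85%). A 7% rate gives 5.6% against 30%, and 0.2% against 13%.

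**Step 4: the significance level.** Pocock's nominal level for three looks (two interim and one final) at two-sided 0.05 is 0.0221, so 0.022 is correct. Counts at the stated 7.5% threshold meet it: 14 against 2 gives Fisher p=0.003, and 15 against 3 gives 0.006. Counts at the 5% example depend on the test: 10 against 2 gives Fisher 0.035 but pooled z 0.018; 9 against 2 gives 0.061 and 0.032. At the first look, 5 against 0 of 50 gives Fisher 0.056 and z 0.0218. The protocol does not name the interim test.

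**The case against.** The best defence is that this is advice to a DSMB and not a rule. The protocol says so, lowers the threshold for more serious events, and allows extra analyses and an earlier second look. Other safeguards do not use these percentages: the coordinating centre reviews adverse event reports within 24 hours, the DSMB is told at once of unanticipated, possibly related Grade 3-4 events, and it reviews all on-treatment deaths. The second-look sentence could also be read as listing one threshold for each outcome, since the goal, the unblinding text and the step-wise actions all use *or*. On that reading *and* is a drafting slip.

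Most of this stands, and it limits the consequence. A reader might infer that the DSMB could not act on toxicity alone at the second look; the documents do not support that. It does not remove the inconsistency. The protocol itself refers to these criteria as stopping rules, and non-binding guidance still needs to state one figure. It could be argued that the 5% example concerns stopping the trial and not dropping an arm. But it counts events in the highest-dose arm, directly parallels the first-look example, and gives no reason for a lower percentage.

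A reader might also see p<0.022 as a third, conflicting trigger. That goes too far. It is given as the level for calling a difference significant and is not stated as a condition for dropping an arm. The value is right, and it agrees with counts at 7.5%. Misses at the smaller counts depend partly on the test chosen. Only its role in the safety guidance is left unexplained.

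**Conclusion.** The second-look guidance is wrong as written on two counts. The event count belongs to a 5% difference while the stated threshold is 7.5%: 9-10 events against 14-15 in one arm, and 18-20 against about 28-30 in both. At true rates of 2% and 10% this is the gap between about 87% and 54% of trials reaching the mark. The connective also differs from the first look and from the text before and after it.

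The effect of *and* depends heavily on completion. With 2% against 10% events, the joint rule is met in about 26-33% of trials (65-70% under *or*) if the other high-dose participants complete at 75%, and in about 1.5-3% (54% under *or*) if they complete at 85%. These figures assume that every event is a non-completion, which follows closely from a safety outcome defined by permanent discontinuation. Participants who stop after taking enough doses would still count as completers, which would lower the *and* figures. Treating events and completion as independent would exaggerate the loss. Clustering is ignored.

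This should be fixed, but it is a defect of wording in advisory guidance. It does not show that the DSMB is prevented from acting.

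**What to change.** Reconcile the text under Interim analyses so that each look has one adverse event difference, with the single-arm and two-arm event counts computed from that figure. Join the adverse event and completion criteria in the same way in the goal, both looks, the unblinding text and the step-wise actions. Which difference and which connective apply is for the sponsor and the DSMB to settle; this review does not choose them.

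As a minor clarification, state whether p<0.022 applies to the safety guidance and, if it does, with which test.

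The cost is a wording amendment and a matching note to the DSMB, with no new data or participants. It is useful only if made before the second interim analysis.

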# Randomization

Randomization will be by individual, except if there are more than one participant from the same household. If a HHC is enrolled and belongs to the same household as someone who has already been enrolled and randomized, that HHC (and all subsequent HHC from the same household) will be allocated to the same regimen *as long as they are enrolled within 14 days*. If they are enrolled later, they will be excluded. This is to avoid preferential enrollment of patients in the same household who may deem one regimen more attractive than the other, as was seen in our earlier 4R vs 9H trial.

Randomization will be computer generated and web-based. Investigators will enter all information from the initial case report form (baseline CRF). The randomization program will verify eligibility, and whether another member of the same household has already been randomized. Randomization will be in blocks of variable size, and stratified by country, and within Canada by city. The web based programme will be developed by collaborators ([name] and team) at the Laboratoire de télématique biomédicale (LTB) du Réseau en santé respiratoire du Québec (RSR), Sherbrooke, QC, who were responsible for all web-based data entry, randomization and adjudication panel work in our prior multi-centres trials (for demo see 2R^2^ link: [http://2r2-demo.crc.chus.qc.ca](http://2r2-demo.crc.chus.qc.ca/)  ID: 2r2demo Password: demo)

